### Data collection and management

Participating centres completed the following case report forms (CRFs):
Eligibility checklist prior to or at the time of randomisationPre-treatment and tumour assessment at baseline prior to cycle 1Treatment forms on day 1 of each chemotherapy cycle (cycles 1–4 or 6). The data collected included PS, protocol treatments received, toxicity and reasons for reduction/delay/omission of treatmentToxicity forms at the end of each cycle given, prior to next cycle and 30 days after completion of the last cycle of chemotherapyRadiotherapy worksheet during and after completion of RTPost treatment form 30 days after the last cycle of chemotherapyFollow-up forms at each follow-up visit starting at 3 months postcycle 4 (or 6) visit (continuing 3 monthly until 12 months and then 6 monthly thereafter)Serious adverse event (SAE) forms used to report all SAEsProgression/relapse/death forms to report the patient status.

Copies of all CRFs continue to be returned to the trials centre for statistical analysis. All forms are tracked and entered into a study-defined database for which consistency checking is programmed in. Data managers check for missing and invalid data using SQL queries and statistical programmes. Any queries raised are returned to the centres for correction or clarification.

On completion of the study, the data will be written onto compact disk and archived in a safe and secure location within the MAHSC-CTU. Paper copies of the CRF's will be retained at sites for at least 15 years following the last, patient entered or, if all are deceased may be archived off site. All paper data will be destroyed after 15 years on the approval of the chief investigator.

The trials centre staff are in regular contact with local centre personnel to check on progress and to help with any queries that may arise. Incoming forms are checked for completeness, consistency, timeliness and compliance with the protocol.

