### Statistical analysis plan

The analysis will be based on intention-to-treat principles (ITT). Patient data will be grouped by treatment arm according to the treatment assignments made via the MAHSC-CTU randomisation line. The primary data analysis is planned for January 2015.

The stratification factors include centre, PS (0–1 vs 2) and biochemical factors (eg, LDH, sodium, alkaline phosphatase). Comparison of data by centre will be scrutinised to identify any data inconsistencies, it will also be used to identify those centres planning to give either four or six cycles of chemotherapy. Analysis will be carried out to identify any differences between the two schedules. Other factors have been identified in previous studies to be prognostic factors and will be used to calculate the Manchester score, which gives three groupings of good, intermediate and poor prognosis; these scores will be used to compare OS and response rate.

The only planned interim analyses have been performed for the Independent Data Monitoring Committee (IDMC). Reports have been submitted to the IDMC on an annual basis starting 12 months after the first patient was randomised.

The following are the qualifications for analysis of time-to-event efficacy parameters:
All randomised patients will be included in the analysis of overall survival (OS) and local progression free survival (ITT).

OS is the time between date of randomisation and date of death of any cause. Survivors will be censored on the last date known to be alive. Local progression-free survival (local control) will be calculated from the date of randomisation to the date of first clinical evidence of progressive disease at the primary site, or death. Kaplan-Meier curves will be drawn for each treatment group. Overall survival and local progression-free survival will be compared using the Mantel-Cox version of the log rank test.
All randomised patients treated with at least one study dose of cisplatin and etoposide will be included in the comparison of proportions of grade 3 and 4 toxicities.

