Toxicity will be assessed according to NCI Common Terminology Criteria for Adverse Events V.3.0. The proportion of patients experiencing a grade of 3 or above acute toxicity, including acute and/or late radiation morbidity, will be compared between the treatment groups using χ^2^ and Fisher Exact tests. Acute toxicity will be defined as toxicities occurring from commencement to 3 months after completion of treatment; late toxicity will be defined as toxicities occurring between 3 months and 2 years after completion of treatment.

All patients treated with at least one dose of cisplatin and etoposide will be evaluated for tumour response and included in the analysis of tumour response rates. Response will be assessed according to Response Evaluation Criteria In Solid Tumours (RECIST) criteria. The proportion of patients in each treatment group whose best response (up to approximately 28 days postcycle 4 or, if stopped prior to cycle 4, approximately 28 days after last chemotherapy cycle given) from randomisation is complete or partial will be compared using χ^2^ and Fisher Exact tests.

Safety analyses will be performed for all randomised patients treated with at least one dose of chemotherapy. Adverse effects will be summarised and compared between the two arms.

The relative chemotherapy and RT dose intensity (RDI) will be summarised by calculating the median, SD, IQR and range for patients in each randomised treatment group. The RDI will be compared between the treatment groups by using the Wilcoxon Rank Sum test.

A detailed description of patient disposition will include a summary of the following:
All patients entered and enrolled: overall, by treatment arm and by countryReasons for patients entered but not enrolledAll enrolled patients treated with study drug, by treatment armReasons patients enrolled but not treated with study drugReasons patients discontinued study drug treatmentAll important protocol violations.

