### Safety reporting

Data were collected at each trial visit regarding any SAEs (as defined by Good Clinical Practice Guidelines). All SAEs causally related to either chemotherapy or RT treatment were reported to the MAHSC-CTU and followed until they resolved or stabilised. Late radiation toxicities continue to be recorded at each follow-up visit (according to the CTCAE V.3.0 grading system).

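### The severe-toxicity comparison is stated with two grade rules (3–4, and 3 or above), and its acute proportion takes in late events that the plan defines as separate

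*Protocol article*

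**What the plan says.** The Abstract and the Methods and analysis section of the Protocol article both list acute and late toxicity, graded by CTCAE V.3.0, among the secondary outcomes compared between arms.

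The Statistical analysis plan section describes the comparison twice.

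- In the list of analysis populations, randomised patients given at least one dose of cisplatin and etoposide "will be included in the comparison of proportions of grade 3 and 4 toxicities".
- In the toxicity paragraph that follows, with χ² and Fisher exact tests named: "The proportion of patients experiencing a grade of 3 or above acute toxicity, including acute and/or late radiation morbidity, will be compared".

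The same paragraph then gives two windows that do not overlap: "Acute toxicity will be defined as toxicities occurring from commencement to 3 months after completion of treatment", and "late toxicity will be defined as toxicities occurring between 3 months and 2 years after completion of treatment".

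On serious adverse events, Data collection and management lists serious "adverse event (SAE) forms used to report all" such events. Safety reporting says "Data were collected at each trial visit regarding any SAEs", and then "All SAEs causally related to either chemotherapy or RT treatment were reported to the MAHSC-CTU".

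**The concern.** Two things in the toxicity paragraph cannot both be followed as written.

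First, the two grade rules differ by grade 5, which is fatal toxicity. Under the narrower rule, a patient whose only severe event was a fatal one is counted with the patients who had no severe toxicity. All-cause survival still records the death, but it does not show toxic deaths by arm, and that is what a reader of a toxicity comparison between two radiotherapy schedules would look for.

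Second, the proportion labelled acute contains events that the plan's own definition places outside the acute window. The research question asks about acute and late toxicity, yet the only graded comparison stated mixes them. A pooled proportion can hide opposite differences in the two windows. It also mixes a period that nearly all treated patients enter with one that only survivors can complete. The Sample size calculation section plans for 2-year survival of 44% against 56%. If that held, more once-daily patients would live long enough to have a late event recorded.

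**Working it through.** The article gives no toxicity rate and no power for a toxicity comparison, so there is no figure of the plan to reproduce. The check is of the text, with one illustrative calculation.

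**Step 1: grade rule.** Assume that a patient counts if any event of a named grade occurs.

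| Patient's toxicity | Grades 3 and 4 | Grade 3 or above |
|---|---|---|
| None of grade 3 or above | no | no |
| Grade 3 or 4, none of grade 5 | yes | yes |
| Grade 3 or 4, and also grade 5 | yes | yes |
| Grade 5 only | **no** | **yes** |

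Only the last row differs.

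**Step 2: size of that row.** Inputs:

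- Patients randomised: 547 (Setting, Sample size calculation and End of the trial). The Abstract prints 447; the figure that three sections share is used here.
- Patients per arm at 1:1: 547 / 2 = 273.5, taken as 273.
- Share with fatal toxicity: not given in the article; assumed 1–3%.

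Patients per arm affected = 273 × share:

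- 1%: 273 × 0.01 = 2.7
- 2%: 273 × 0.02 = 5.5
- 3%: 273 × 0.03 = 8.2

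These are upper limits for each assumed share, for two reasons. A patient with another grade 3 or 4 event still counts under both rules. The denominator is also all randomised patients, whereas the comparison is limited to treated patients.

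If the share were equal in both arms, the level of each proportion would fall but the difference between arms would not change. If it were 1% in one arm and 3% in the other, the difference would move by 3 − 1 = 2 percentage points.

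**Step 3: windows.**

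| Radiation morbidity of grade 3 or above | Window by the plan's definition | In the compared acute proportion? |
|---|---|---|
| Start of treatment to 3 months after its completion | acute | yes |
| 3 months to 2 years after completion | late | yes |

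The second row contradicts the definition. No sentence in the section states a comparison restricted to the late window. The data for one exist, because Safety reporting says that late radiation toxicities are recorded at every follow-up visit.

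**Step 4: serious adverse events.** Data collection and management has forms for all of them and says that copies of all case report forms go back to the trials centre. Safety reporting says that data were collected on any such event, then describes the related ones as reported to the trials unit and followed to resolution. It does not say that only related events were reported. The statistical section names no arm comparison based on serious adverse events, and its general comparison of adverse effects carries no attribution filter.

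**The case against.** The best defence on the grade rule is that the sentence ending in grades 3 and 4 is there to say who is analysed. The sentence that defines the outcome and names the tests comes shortly after it and includes grade 5. Most analysts would follow the second. That stands, and it is why the risk is conditional. It does not remove the inconsistency, since nothing says which sentence governs.

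On the windows, the defence is that the phrase is clumsy shorthand for two comparisons, and that the layout of tables belongs in the full protocol or an analysis plan not shown here. The second half is fair as to layout. But the phrase as printed puts late events into an acute proportion, and that is a contradiction in this text, not a detail left out. It is also true that mixing windows removes no event, so this part concerns interpretability and not lost data.

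Two stronger readings are tempting. A reader might infer that every fatal toxicity is misclassified. The text does not support this: it needs the population sentence to override the outcome sentence, and even then patients with another grade 3 or 4 event still count. A reader might also infer that unrelated serious adverse events never reached the trials unit, so that attribution by unblinded investigators could bias the arm comparison. That depends on the word 'only', which is not in Safety reporting. Collection of any such event and the return of all forms are stated, and no arm comparison based on serious adverse events is described from which they could be lost.

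**Conclusion.** The concern holds for the toxicity comparison. The grade rule is stated in two ways that differ by grade 5, and the acute proportion includes late events that the plan defines separately, with no late comparison stated although it is a named secondary outcome.

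The grade inconsistency matters only if the narrower wording is applied. It would then affect at most about 3 to 8 patients per arm, on an assumed fatal-toxicity share of 1–3% that does not come from the article. The effect of pooling the windows cannot be sized from the article.

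No attribution bias in serious adverse events is shown; at most, the two sections that describe their reporting could be worded alike. The primary overall survival analysis is untouched.

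**What to change.** 1. In the Statistical analysis plan section, write grade 3 or above (3–5) in both the population statement and the toxicity paragraph.
2. Delete the words 'and/or late' from the acute comparison.
3. Add one sentence saying that toxicity of grade 3 or above is compared separately for the acute and the late window, as already defined, with the tests already named.
4. Optionally, word Data collection and management and Safety reporting consistently on which serious adverse events reach the trials unit.

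Items 1 to 3 change a few lines in one section and need no new data. Item 4 is a clarification in two sections. The split gives two toxicity comparisons where one was stated, which suits a secondary outcome that already names both.

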### Changes to the protocol after the start of the trial

The trial details documented here are consistent with CONVERT trial protocol V3 (dated: 10 June 2008). There were no significant changes to the protocol after the start of the trial, only minor administrative amendments and clarifications have been made during the course of the trial.

### End of the trial

The trial will end once all 547 patients recruited have died or completed 5 years of trial follow-up (whichever is sooner).

## Ethics and dissemination

### Radiotherapy quality assurance

The trial is subject to a RT quality assurance programme, managed by the National Cancer Research Institute Radiotherapy Trials Quality Assurance Team (RTTQA). Participating centres were provided with RT planning guidelines, including an atlas of organ at risk delineation, and had to pass an initial assessment before patients could be randomised into the trial, and there were further assessments afterwards.

The initial assessment consisted of:
Completion and return of a questionnaire detailing the RT facilities available to the centreReturn of two RT treatment plans for a patient with limited-stage SCLC, previously treated in the centre with radical intent, who satisfied the eligibility criteria for CONVERT and had been replanned according to the CONVERT protocol for each treatment arm: 66 Gy in 33 daily fractions once-daily and 45 Gy in 30 fractions twice-daily

During the trial, plans were randomly requested from each centre as part of the continuing quality assurance programme and feedback was provided in case of protocol deviations. Participating centres had to agree to address uncertainties revealed by the quality assurance programme.^16^

### Safety reporting

Data were collected at each trial visit regarding any SAEs (as defined by Good Clinical Practice Guidelines). All SAEs causally related to either chemotherapy or RT treatment were reported to the MAHSC-CTU and followed until they resolved or stabilised. Late radiation toxicities continue to be recorded at each follow-up visit (according to the CTCAE V.3.0 grading system).

### Early stopping of trial treatment

Protocol treatment may be stopped in the following instances:
There is evidence of progressive disease according to RECIST criteria on CT scan (see online supplementary appendix 4)Unacceptable toxicityEarly toxicity assessment (after 20 patients have completed treatment in each arm), which, for safety reasons, will be carried out. Data will be reviewed by the Trial Management Group (TMG)Intercurrent illness exists that, in the clinician's opinion, would require discontinuation of protocol therapy.Subsequent histological/cytological review is contrary to the original diagnosisPatient's request.

### Trial monitoring and oversight

No formal on site data monitoring activities were performed as part of the CONVERT trial.

Data are reviewed annually by an IDMC, consisting of three clinicians not entering patients into the trial, and an independent statistician. Throughout the duration of the trial, the IDMC has recommended whether the accumulated data from the trial, together with results from other relevant trials, justified continuing recruitment of further patients. The IDMC has made confidential recommendations to the Trial Steering Committee (TSC).

The role of the TSC has been to act on behalf of the funder, to provide overall supervision for the trial, to ensure that it is conducted in accordance with GCP and to provide advice through its independent Chairman. This independent committee reviews the recommendations from the IDMC and decides on continuing or stopping the trial or modifying the protocol. The Trial Management Group coordinates and manages the trial's day-to-day activities. The TMG is comprised of health professionals and members of the direct study team.

### Dissemination

Data from all centres will be analysed together and published as soon as possible. Individual participants may not publish data concerning their patients that are directly relevant to questions posed by the trial until the TMG has published its report. The TMG will have access to the final data set, form the basis of the Writing Committee and advise on the nature of publications. The trial will be publicised at regional and national conferences. The final results will be presented at scientific meetings and published in a peer-reviewed journal (authorship will be according to the journal's guidelines).
